## Abstract

**Background:**

Heart failure with reduced ejection fraction (HFrEF) is progressive and pervasive. Guidelines provide evidence-based recommendations to manage HFrEF, yet adherence to Guideline Directed Medical Therapy (GDMT) is low. An opportunity exists to improve adherence by delivering actionable data, reducing clinician information overload, and enhancing patient care. A Pragmatic Trial Evaluating the Impact of the Anumana Clinical Decision Support Tool for Guideline-Directed Management of Heart Failure (ACT-HF) will evaluate a clinical decision support software (CDSS) that integrates in electronic health records (EHR), automates chart review, and identifies care gaps.

**Methods:**

Anumana's Guideline Navigator is an innovative, multi-module AI-enabled CDSS with automated chart review to rapidly analyze EHR data, detect care gaps, and provide alerts for eligible patients not receiving optimal GDMT. ACT-HF, a multi-center cluster pragmatic trial, will recruit and randomize clinician participants (≤250) from 2 health systems to receive intervention software or provide usual care. The trial will evaluate outpatient care for adults with documented HFrEF and not on optimal GDMT (>2148). Outcomes will be evaluated at 90 days. Clinician participants may discuss results with patients, but patients will not have access to the CDSS.

**Results:**

Primary outcome is change in GDMT medications; exploratory endpoints include clinical outcomes, resource utilization, and usability. Subgroup analyses include health system, clinician, and patient-level characteristics associated with outcomes.

**Conclusion:**

Building on efforts to improve GDMT adherence, ACT-HF will test Anumana's Guideline Navigator in a multicenter study to evaluate outcomes and further refine the CDSS EHR integration EHR for improved clinical utility, workflow integration, and patient outcomes.

## Background

1

Heart failure (HF) is a progressive condition and a leading cause of morbidity and mortality globally. In 2021, HF was the underlying cause in more than 85,000 deaths and contributing cause in more than 420,000 deaths; the prevalence of HF is projected to be 3 % of the US population in 2030 [1].

HF contributes significantly to healthcare resource utilization. Specifically, there were >8 million physician office visits for HF in 2019 and >1.3 million visits to the emergency department for HF in 2020 in the US [1]. The overall cost of HF is projected to increase 127 % from an estimated $30.7 billion in 2012 to $69.8 billion in 2030; with an estimated annual cost of $24,383 per HF patient; 65 % of the cost is HF hospitalizations ($15,879) [1].

The current Clinical Practice Guidelines provide evidence-based pharmacological recommendations for management of HF with reduced ejection fraction (HFrEF); Guideline Directed Medical Therapy (GDMT) [2] provides the highest level of recommendations for 4 classes of pharmacotherapy, or “quad-therapy”, for patients with HFrEF, including medications from each of the following classes: renin-angiotensin-aldosterone system inhibitors (RAASi), beta blockers, mineralocorticoid receptor antagonist (MRA), and sodium-glucose cotransporter 2 inhibitor (SGLT2i) [2]. A recent analysis of patients hospitalized with heart failure revealed that an estimated 82 % of patients with newly-diagnosed HFrEF are eligible for GDMT, but only ~15 % were prescribed quad-therapy [3].

Declines in HF mortality are primarily attributable to evidence-based approaches to managing patients with HF. GDMT is estimated to reduce cardiovascular mortality and HF hospitalization by approximately 62 % and results in 1.4–6.3 additional years of life, compared to limited conventional therapy [1].

Despite the recommendations, adherence to GDMT for HFrEF remains low [4,5]. Several potential contributing factors to this low adherence have been identified, including gaps in clinician knowledge, patience reluctance, and cost [6]. Among patients with Medicare drug plan coverage, the median monthly out-of-pocket (OOP) costs of quad-therapy is calculated at $94, compared to the $3 median monthly cost of triple-therapy with a substitution for the RAASi medication from the first-line therapy to the second-line generic [7]. Further, a recent cost analysis reported that the use of quad-therapy for HFrEF is cost effective compared to triple-therapy and double-therapy [8]. Also, a trial is currently underway to evaluate outcomes when cost is considered in a shared-decision making model [9].

A Pragmatic Trial Evaluating The Impact Of The Anumana Clinical Decision Support Tool For Guideline-Directed Management Of Heart Failure (ACT-HF) Study is designed to evaluate the clinical impact of a clinical decision support software which integrates within the electronic health record (EHR) to provide automated chart review and highlight GDMT care gaps to clinicians during routine outpatient care.

## Overview of ACT-HF trial design

2

ACT-HF is a multi-center cluster-randomized behavioral-intervention trial that will recruit and randomize clinicians to receive access to the intervention software (Anumana's Guideline Navigator) or provide usual care.

Clinicians (≤250) will be recruited from 2 health systems to participate in the ACT-HF Study. Participants will be clustered at the care team level within each site. The trial will evaluate the clinical care provided during >2148 eligible clinical encounters and 90 days following the index encounter. Clinicians will be consented and randomized into intervention or care as usual; patients are not recruited for this study (Fig. 1).

**Fig. 1 f0005:**
[figure not shown]
CONSORT diagram of general study design.

The primary study endpoint to be evaluated is change in GDMT medications, with exploratory endpoints evaluating other clinical outcomes. Subgroup analyses will be conducted to evaluate the health system, clinician, and patient-level characteristics associated with outcomes.

The study has received a waiver of informed consent through a central institutional review board (IRB) review (WCG Clinical Services, Princeton, NJ). The study is sponsored by Anumana, Inc. The study investigators and authors are responsible for study design, analysis, and publications.

## Study population

3

ACT-HF is designed to evaluate the impact of an interventional software (Guideline Navigator) on clinical decision making in ambulatory care for HFrEF. Clinicians who medically manage patients with HFrEF are recruited and consented to participate in the ACT-HF study; patients are not recruited as participants in this study.

Eligible clinical encounters for the interventional study include clinical encounters with adult patients who have a diagnosis of HFrEF or a documented LVEF ≤40 %, and who are not presently on optimal GDMT. Clinical encounters will not be eligible for those patients who are in hospice care, who are pregnant, who are already receiving optimized GDMT, or for those patients who have opted out of EHR-based research.

Participating clinicians randomized to the intervention group will receive a notification when the intervention software has identified a patient record suboptimal GDMT prescribing. The clinician will choose whether and how best to inform the patient of the notification and potential changes to their care plan; individual patients will not have access to the intervention software or results. Guideline Navigator will not evaluate records of patients who do not meet eligibility criteria and no alerts will be provided.

## Study intervention software

4

Anumana has developed an innovative AI-enabled clinical decision support system - Guideline Navigator which is a multi-module software solution with a user interface. Guideline Navigator connects with the electronic health record (EHR) through an application program interface (API) to (1) rapidly analyze patient clinical data (2) harmonize structured data, (3) curate unstructured clinical notes with natural language processing (NLP), (4) interpret patient data using a Bidirectional Encoder Representations from Transformers (BERT) model to complete an automated chart review, (5) evaluate alignment to guideline directed medical therapy (GDMT) for heart failure with reduced ejection fraction (HFrEF) using a machine learning model trained to identify eligible patients with potential gaps in care, (6) identify relevant indications and contraindications, (7) summarize potential GDMT gaps-to-care with a point-of-care user interface for clinicians to review, and (8) trigger a point-of-care alert to notify clinicians of potential opportunities to optimize clinical care for patients with HFrEF (Anumana, data on file).

Guideline Navigator software is integrated within each participating health system's EHR and access is restricted to the participating clinicians. For the purposes of the ACT-HF study, Guideline Navigator will process the EHR data for eligible clinical encounters on the night prior to an appointment; clinicians may also reprocess the results at point-of-care to incorporate any updated prescription information that was made during patient check-in. A wrong recommendation will not be considered an adverse event, unless there is an event as a consequence of such. All others will be considered errors, but not adverse events. Clinicians randomized to the intervention group receive an alert (Fig. 2) for any eligible encounter with actionable results from the Guideline Navigator software; there is no alert for ineligible clinical encounters or for clinicians randomized to the standard of care group. The clinician may receive multiple alerts for a patient for a return patient who remains non-compliant with GDMT during the study period.

**Fig. 2 f0010:**
[figure not shown]
EHR-based alert display.

## Study data collection

5

Study data will be collected from participant surveys, study software metrics, and EHR data as a read-out for clinician decision-making. Surveys were designed by experts in computer-human interaction and healthcare delivery research to quantitatively assess knowledge, readiness, usability, and acceptance of the software with questions designed to evaluate decision-making behavior, clinician sentiment towards technology-based clinical decision support solutions, and clinical inertia.

Clinician participants may discuss results with patients; however patients will not have direct contact with the study team or direct access to the ACT-HF Study software or software output. Guideline Navigator will only provide recommendations for HFrEF patients who are not currently prescribed optimal GDMT.

EHR data will automatically be collected in a privacy-preserving manner and all data will be deidentified and analyzed in the aggregate, to avoid accidental disclosure of protected health information (PHI). EHR data will be evaluated at the Index Encounter and 90-days following the Index Encounter to evaluate whether there were any changes in treatment patterns in both control and intervention groups. Pre-study surveys will be conducted to evaluate clinicians' knowledge of GDMT and their readiness to adopt the new technology. Post-study surveys will be conducted to further examine usability and acceptance of the CDS software.

## ACT-HF study endpoints

6

Clinical outcomes data will be collected as described for the primary endpoint; participating clinicians will not be required to manually upload any clinical outcomes data, as these will be abstracted from the EHR by a clinical research coordinator. Software related data, including software-based study survey data, will be linked to clinical encounter data through a deidentified encounter ID associated with the participating provider. No identifiable patient data will be uploaded into the electronic data capture (EDC) system.

Outcomes of interest in the ACT-HF study are shown in Table 1. The primary outcome of the ACT-HF Study is to evaluate the total number of GDMT-HF-recommended HFrEF medications prescribed at 90-days post clinical encounter, per patient, compared to care-as-usual (control arm). Exploratory endpoints will be evaluated in three categories: clinical outcomes, intervention software CDS outcomes, and patient outcomes. At the completion of the study, subgroup analyses will be conducted to evaluate the impact of the Intervention software by factors such as clinical setting, clinician factors, and patient factors.

**Table 1 t0005:** ACT-HF study endpoints.

ACT-HF Study - Primary endpoints
• Number of GDMT-recommended medications for HFrEF prescribed at 90-days post clinical encounter, per patient, compared to care-as-usual (control arm)

ACT-HF Study - Exploratory endpoints		
Clinical outcomes	Software usability outcomes	Patient outcomes
• Change in patient NYHA Class from baseline through observational period • % of patients taking optimal GDMT-HF therapy based on software-identified indications and lack of contraindications • Time to start of new GDMT-HF medication class • Dosage of GDMT-HF-recommended quad therapy HFrEF medications reached • % of patients for whom at least one GDMT-HT medication was prescribed.	• User engagement with the software, including session counts, session duration, and report button click counts. • Percent of notification prompts that are accepted or dismissed, at the clinician level. • Clinician experience with software (survey-based) o Cognitive behavioral, and contextual factors related to clinician satisfaction, acceptance, and use of the software o Reasons for rejecting, modifying, or ignoring recommendation o Barriers and facilitators to use	• Changes in BNP or NT-pro-BNP, blood potassium, blood creatinine, and estimated glomerular filtration rate • Hospitalizations o Heart Failure o All-cause • Mortality o Heart Failure o All-cause • Indicators of resource utilization o Ordering of echocardiogram, time from index encounter, and echocardiogram results o Outpatient appointments o Specialist visits o Hospital days o Emergency room visits o 30 day readmissions following a heart failure hospitalization

ACT-HF Study - Safety endpoints
• Incidences and event rates of study-related adverse events (AE), compared to control arm • Incidences and event rates of study-related Severe Adverse Events (SAE), compared to control arm

Adverse events (AE) and severe adverse events (SAE) will also be reported throughout the duration of the study, as applicable. For the purposes of the ACT-HF study, adverse events include death, side effects or allergies to a medication that was started due to a failure of the software to identify prior side effects or allergies and the clinician fails to check for prior side effects or allergies, or other reportable events. ACT-HF is a minimal risk study and AE/SAEs are not anticipated. If any AE/SAE occurs during the study, clinician participants are asked to notify the Site PI or designee to report the event within 24 h of knowledge of the event.

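### The exploratory 'optimal GDMT' endpoint takes the tested software's own indications and contraindications as its standard, so it measures concordance with the software and leans towards the intervention by an unknown, probably small amount

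*Protocol article*

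**What the plan says.** The section on ACT-HF study endpoints puts the exploratory endpoints in three groups: "Exploratory endpoints will be evaluated in three categories: clinical outcomes, intervention software CDS outcomes, and patient outcomes". In Table 1 the clinical group includes the percentage "of patients taking optimal GDMT-HF therapy based on software-identified indications and lack of contraindications".

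The section on the study intervention software gives, as one of the software's functions, "6) identify relevant indications and contraindications". Clinicians in the intervention group "receive an alert (Fig. 2) for any eligible encounter with actionable results from the Guideline Navigator software", whereas "there is no alert for ineligible clinical encounters or for clinicians randomized to the standard of care group".

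The adverse-event definition below Table 1 foresees a side effect or allergy to a drug "started due to a failure of the software to identify prior side effects or allergies". It adds a second condition: the clinician must also have failed to check. The software section treats a wrong recommendation with no resulting event as an error, not an adverse event.

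The endpoints section says participating clinicians need not upload clinical outcomes data, "as these will be abstracted from the EHR by a clinical research coordinator". It does not say that the coordinator, or anyone else independent of the software, judges indications or contraindications.

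The primary endpoint is the number of recommended medications per patient at 90 days, with no reference to the software's list.

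**The concern.** The device under test supplies the standard by which part of its own effect is judged. A contraindication that the software overlooks leaves the drug inside the software's definition of optimal therapy. A clinician who follows the alert is then credited, and one who finds the intolerance and withholds the drug is marked down. The rule may be identical in both arms, but only one arm is steered towards it.

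The endpoint is listed under clinical outcomes, not under software usability, and it is the only endpoint in Table 1 that mentions contraindications. A reader who asks whether the additional prescribing was appropriate would turn to it, and it cannot answer that independently. No endpoint in Table 1 counts starts against a charted contraindication that cause no event, so such a start could appear only as a favourable result.

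**Working it through.** The article states no figure for this endpoint and no accuracy for the software, so there is nothing to reproduce. The check is of direction, with assumed inputs.

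**Model.** Each patient has one open drug class, and filling it would complete optimal therapy.
- c: share of patients truly contraindicated for that class
- m: share of those whom the software misses
- r0, r1: prescribing to the missed patients in the control and intervention arms
- d: arm difference in prescribing to truly eligible patients

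Patients whose contraindication the software recognises are assumed to be treated alike in both arms.

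**Step 1: no true benefit (d = 0).** An independent standard that gives no credit for starting a contraindicated drug shows a difference of 0. Software scoring shows:
- over all patients: c × m × (r1 − r0)
- over patients the software regards as eligible: c × m × (r1 − r0) / [(1 − c) + c × m]

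| c | m | r0 | r1 | All patients | Software-eligible only |
|---|---|---|---|---|---|
| 5% | 5% | 2% | 10% | 0.0025 × 8 = 0.02 points | 0.02 / 0.9525 = 0.02 points |
| 10% | 20% | 2% | 20% | 0.02 × 18 = 0.36 points | 0.36 / 0.92 = 0.39 points |
| 20% | 30% | 2% | 40% | 0.06 × 38 = 2.28 points | 2.28 / 0.86 = 2.65 points |

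The result is exactly 0 if m = 0 or r1 = r0. It is positive whenever m > 0 and r1 > r0, and r1 > r0 is what one expects when only one arm is prompted.

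**Step 2: with a true benefit.** Assume c = 20%, m = 20%, d = 30 points and r1 − r0 = 25 points. Then 1 − c = 0.80 and c × m = 0.04.
- Software scoring, all patients: 0.80 × 30 + 0.04 × 25 = 25.0 points.
- Independent standard, all patients, contraindicated starts not credited: 0.80 × 30 = 24.0 points.
- Independent standard, all patients, withholding also credited as optimal: 24.0 − 0.04 × 25 = 23.0 points.

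On the same patients, software scoring exceeds the independent standard by 1.0 to 2.0 points under these inputs.

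**The case against.** **The bias may be dilution, not inflation.** If clinicians respond to false gaps no more than to true ones, the software-scored difference is an average of the two responses. With the Step 2 inputs, among software-eligible patients it is 25.0 / 0.84 = 29.8 points, against 24.0 / 0.80 = 30.0 among truly eligible patients. The arithmetic is right, but it compares two different sets of patients. On the same 84% of patients the independent result is 24.0 / 0.84 = 28.6. Over all patients, which is how the endpoint is worded, it is 25.0 against 24.0 or less. The direction stands.

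**The scenario is narrower than it first looks.** This stands. A missed contraindication scores as success only if the drug is then prescribed. The adverse-event definition also requires that the clinician failed to check. A patient who reacts and stops the drug may no longer count as taking it. Patients with other open gaps would dilute the effect.

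**Reprocessing.** A reader might infer that the standard can be updated in one arm only, because "clinicians may also reprocess the results at point-of-care to incorporate any updated prescription information that was made during patient check-in". The text does not support this. It ties reprocessing to prescription information and does not say which software run is used for scoring.

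**Harm counted as benefit, or a compromised main result.** A reader might infer either. Safety events are a separate comparison between arms, and the primary endpoint does not use the software's list. One patient could in principle be both an adverse event and an optimal-therapy success, but nothing shows how often.

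**The article is condensed, and the endpoint openly says it is software-based.** Which run is scored, and whether the software was validated, may well be in documents not shown; neither is held against the plan. The standard itself, however, is stated in Table 1. Coordinator abstraction governs how data are captured, not what counts as optimal.

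**Conclusion.** The point holds for one exploratory endpoint. As defined, it measures concordance with the software, and for missed contraindications the error favours the intervention if intervention clinicians act on them more often than control clinicians. The documents do not allow the amount to be quantified. Under the assumed ranges (c 5% to 20%, m 5% to 30%, r0 2%, r1 10% to 40%, one open class per patient) it is 0.02 to 2.28 points of all patients, or 0.02 to 2.65 points of software-eligible patients. It is probably small.

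The documents do not support saying that every kind of software error favours the intervention, or that the trial's primary result is affected. The endpoint should be changed before it is read as evidence of appropriate care.

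**What to change.** 1. In both arms, score optimal GDMT by one prespecified rule applied to the index and 90-day EHR data, independent of software output and blind to arm. The clinical investigators must define what counts as a contraindication; no definition is proposed here.
2. Keep the software-scored version, relabel it as concordance with the software, and report it beside the independent one.
3. Report, by arm, the number of patients started on a class for which the chart already recorded a contraindication or intolerance.

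The cost is one scoring rule and some programming. EHR data are already evaluated in both arms at index and 90 days, and randomisation, intervention and primary endpoint stay unchanged.

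The remedy has a limit of its own. The software reads unstructured notes, and a rule based on structured data may miss contraindications recorded only in free text. The miss may be unequal between arms: intervention clinicians are shown the free-text contraindications that the software finds, may withhold the drug, and would then be scored as failures. Both versions should therefore be shown and this limit stated. Chart review of a random sample, blind to arm and independent of the software, would help to show how large it is.

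### The between-arm comparison of study-related adverse events is not like-for-like, because the only drug-harm event the protocol names cannot arise in the control arm

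*Protocol article*

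**What the plan says.** Table 1 (section 6, ACT-HF study endpoints) lists two safety endpoints: "Incidences and event rates of study-related adverse events (AE), compared to control arm" and "Incidences and event rates of study-related Severe Adverse Events (SAE), compared to control arm".

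The paragraph below the table explains what counts. It begins "adverse events include death, side effects or allergies to a medication" and limits the side-effect and allergy part to "a medication that was started due to a failure of the software to identify prior side effects or allergies", with the further condition that the clinician also did not check. The list closes with "or other reportable events". The paragraph adds that "ACT-HF is a minimal risk study and AE/SAEs are not anticipated" and asks clinician participants to notify the site of any event within 24 h of learning of it.

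Section 4 (Study intervention software) says that clinicians in the standard of care group get no alert. On software errors it says: "A wrong recommendation will not be considered an adverse event, unless there is an event as a consequence of such".

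The exploratory part of Table 1 separately lists heart failure and all-cause mortality, heart failure and all-cause hospitalisation, emergency room visits, potassium, creatinine and eGFR. According to sections 5 and 6, EHR data are evaluated in both groups at the index encounter and at 90 days, and a research coordinator abstracts the clinical outcomes.

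**The concern.** A comparison between randomised arms is informative about harm only if the same event can occur, and be counted in the same way, in each arm. Here the one drug-harm event that is spelled out is defined by its cause, a failure of the intervention software. The safety endpoint also keeps only *study-related* events, and usual care contains no study intervention to which an event could be related.

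The intervention is meant to increase prescribing, so the natural safety question is whether more prescribing brings more adverse effects. A side effect of a drug that the software recommended correctly, or that a control clinician started unprompted, is not named in the adverse event list. A low count in both arms, or a small excess in the intervention arm, would not answer that question, yet a reader could take it as between-arm safety evidence.

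**Working it through.** The article gives no adverse event rate, safety sample size or power, so there is no figure of the plan to reproduce. The check takes each component of the definition in section 6 and asks whether it can occur in control as section 4 describes that arm.

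| Component | Intervention arm | Control arm |
|---|---|---|
| Side effect or allergy to a drug started through a software failure | Possible | Not possible: no alert reaches the clinician |
| Event that follows a wrong recommendation (section 4) | Possible | Not possible: no recommendation is delivered |
| Death | Possible | Possible, but when it is *study-related* is not clear |
| Other reportable events | Possible | Possible, but neither the content nor *study-related* is clear |
| Side effect of a drug started for any other reason | Not named | Not named |

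1. The first two rows compare a possible event with an impossible one. The zero in control assumes that no control patient is also treated by an alerted clinician.
2. Death and other reportable events could give a fair contrast only if counted whatever their cause. The *study-related* qualifier in Table 1 works against that, because most such events under usual care would be judged unrelated.
3. The sentence can also be read so that the software-failure condition governs death. On that reading nearly the whole named list is confined to the intervention arm.
4. Reporting adds to the asymmetry. Clinicians know whether they receive alerts, and only those in the intervention arm have a recommendation to which an event could be attributed.

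A side calculation bears on the statement that events are not anticipated. The article gives no mortality rate, so annual mortality *a* is an assumption. The Abstract gives more than 2148 patients; 2148 is used here.

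Expected deaths in 90 days = 2148 × (1 − (1 − *a*)^(90/365.25))

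- *a* = 5%: 27.0
- *a* = 10%: 55.0
- *a* = 15%: 84.3

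These are deaths from any cause in both arms together. They are illustrative only. They show that the statement cannot refer to deaths of every cause, and they say nothing about software-caused deaths.

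**The case against.** The strongest reply is that the list is open and has three elements, of which only one depends on the software. That stands. A reader might infer that the whole control rate is zero by definition; the text does not support this, because death and other reportable events can occur under usual care.

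A reader might also infer that the trial cannot inform safety, or that potassium and renal changes go unrecorded. Neither follows. Table 1 lists these outcomes, hospitalisation and mortality, and they reach the study through EHR abstraction, not only through clinician reports. What is amiss is that they are labelled exploratory while the comparison labelled safety rests on the other definition.

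The deaths calculation does not prove a contradiction. If the statement about anticipated events means study-related events, which its context allows, then 27 to 84 deaths from all causes do not conflict with it. Nor can one count every death for that purpose while counting only software-caused events to obtain a zero in control.

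The rules on adverse events in sections 4 and 6 can be read together: section 4 separates errors from events, and the open list in section 6 can take in harm from another missed contraindication. Their wording differs, but neither excludes the other.

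Finally, relatedness criteria may sit in a fuller protocol, and the article attaches no test or stopping rule to these endpoints. The absence of such detail is not the point. The comparison with control is stated in the article, and for the named drug-harm component no relatedness rule could make it like-for-like.

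**Conclusion.** The point holds in a limited form. The named side-effect and allergy component is structurally zero in control, and the *study-related* qualifier leaves the status of death and other reportable events under usual care unclear. Together with reporting by clinicians who know their arm, this makes the stated between-arm comparison largely uninterpretable as evidence on harm from alert-driven prescribing.

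The conclusion rests on the wording of sections 4 and 6 and on control clinicians receiving no software output. It does not depend on any assumed event rate. The primary endpoint is unaffected. The intervention-arm count keeps its value as a description of software-caused harm.

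**What to change.** 1. Report software-attributed adverse events, severe adverse events and wrong-recommendation errors for the intervention arm only, descriptively, with exact confidence intervals. Remove the comparison with control from the two safety lines of Table 1, and use one wording for these events in sections 4 and 6.
2. Base the between-arm safety comparison on outcomes already in Table 1, abstracted from the EHR in the same way in both arms over 90 days: all-cause death, all-cause and heart failure hospitalisation, emergency room visits, potassium, and creatinine or eGFR. Analyse them as randomised, with care-team clustering taken into account. Because laboratory values exist only where a test was done, show the number tested in each arm.
3. State that the events described as not anticipated are software-attributed events, since death is on the adverse event list and mortality is an endpoint.

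The cost is a change of endpoint wording and one added table from data already being abstracted.
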